## Secondary Endpoint

Change in an overall indicator of Health-related QOL [SF36 (Acute Version) before and after drug use

1. **Statistical Discussion**
   1. Rationale for Determination of Target Enrollment

On the hypothesis that the use of EMLA Cream will increase VAS score by 10 mm compared with Youpatch Tape and an intra-individual standard deviation in VAS improvement of 20 mm, and with the α for type 1 error (α error) as 5% on both sides and 80% power (1 – β), 31 individuals are required in each group (62 in both groups). Assuming a discontinuation/dropout rate of 5%–10% due to drug-induced side effects and other reasons, the scheduled enrollment was set at 34 individuals per group (68 in both groups).

- 1. Analysis Populations

1. The analysis of the primary and secondary endpoints using the Full Analysis Set constitutes the primary analysis. An analysis using the Per Protocol Set (PPS) will also be performed to confirm the reliability of the analysis results.
   1. Analysis of Endpoints and Methods

Endpoints for analysis

1. Primary endpoint: Comparison of the analgesic effects of EMLA Cream and Youpatch Tape during arteriovenous fistula puncture
2. Secondary endpoint: Change in Health-related QOL [SF36 subscale score (0–100 points)] before and after the use of EMLA Cream and Youpatch Tape

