## 8.2. Schedule for Monitoring, Testing, and Reporting

| Period  Parameter | Consent obtained – determination of eligibility for study enrollment | Pre-observation period (1 week) | Period I (1 week) | Wash out (1 week) | Period II (1 week) |
| --- | --- | --- | --- | --- | --- |
| Explanation of study/obtaining consent | ○ |  |  |  |  |
| Investigation of patient characteristics | ○ |  |  |  |  |
| Examination by doctor | ○ |  |  |  |  |
| Height, weight | ○ |  |  |  |  |
| Temperature, blood pressure, heart rate | ○ | ○ | ○ | ○ | ○ |
| Pain score during arteriovenous fistula puncture measured by VAS (on every occasion dialysis is performed) |  | ○ | ○ | ○ | ○ |
| Health-related QOL measured using the SF36 (acute version) (after final dialysis in that period) |  | ○ | ○ | ○ | ○ |
| Check made for adverse events caused by the interventional drug |  |  | ○ | ○ | ○ |
|  | | | | | |

8.3. Specimen Storage and Use of Specimens by Other Institutions, Etc.

Materials concerning this study stored by the study sites and the Principal Investigator (including records of subject observations, test data, Ethics Committee screening records, and subject consent forms) shall be retained until a date 5 years from the date of completion of the study as a whole or 3 years from the date of final publication of the results of the study, whichever is the later. After the end of the retention period, they are to be disposed of appropriately (shredded or burned).

Specimens such as blood and urine samples will not be collected in this study.

1. **Target Enrollment and Study Period**
   1. Target Enrollment

The target number of applications in this hospital is 20 patients.

The total number of subjects to be enrolled in the study as a whole is 68 patients.

(The study as a whole will include Kanazawa Medical University Hospital, Keiju Medical Center, Anamizu General Hospital, and others)

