**Method of Analysis of Primary Endpoint**

The primary endpoint is analyzed by the standard statistical procedures^18)^ for a two-group, two-period crossover study.

Total effect of EMLA Cream in Group A (E_A1I_) = ΔVAS (Group A EMLA)

Total effect Youpatch Tape in Group A (E_A2C_) = ΔVAS (Group A Youpatch)

Total effect of EMLA Cream in Group B (E_B2I_) = ΔVAS (Group B EMLA)

Total effect Youpatch Tape in Group B (E_B1C_) = ΔVAS (Group B Youpatch)

Crossover design analysis

|  | Period I | Period II | Difference in effects | Sum of effects |
| --- | --- | --- | --- | --- |
| Group A | EMLA  E_A1I_ = T_I_ + P_I_ + TP_A_ | Youpatch  E_A2C_ = T_C_ + P_2_ + TP_A_ | D_A(1 – 2)_ = E_A1I_ – E_A2C_  = (T_1_ – T_C_） + (P_1_ – P_2_) | S_A(1 + 2)_ = E_A1I_ + E_A2C_ = (T_I_ + T_C_) + (P_1_ + P_2_) + 2TP_A_ |
| Group B | Youpatch  E_B1C_ = T_C_ + P_1_ + TP_B_ | EMLA  E_B2I_ = T_I_ + P_2_ + TP_B_ | D_B(1 – 2)_ = E_B1C_ – E_B2I_  = [ – (T_I_ – T_C_)] + (P_1_ – P_2_) | S_B(1 + 2)_ = E_B1C_ + E_B2I_ = (T_I_ + T_C_) + (P_1_ + P_2_) + 2TP_B_ |

E: Total effect: T: treatment effect; P: period effect; TP: treatment–period interaction effects (or allocation effects or carryover effects).

Subscripts: I: EMLA Cream; C: Youpatch Tape; 1: Intervention Period I; 2: Intervention Period II; A: Group A; B: Group B.

(1) Analysis of period effect

D_A(1 – 2)_ – ( – D_B(1 – 2)_) = D_A(1 – 2)_ – D_B(2 – 1)_ = 2(P_1_ – P_2_)

Test whether or not this is 0 by comparing D_A(1 – 2)_ and D_B(2 – 1)_ using an unpaired t-test, and if the difference is not significant the period effect may be ignored.

(2) Analysis of carryover effect

S_A(1 + 2)_ – S_B(1 + 2)_ = 2(TP_A_ – TP_B_)

Test whether or not this is 0 by comparing S_A(1 + 2)_ and S_B(1 + 2)_ using an unpaired t-test, and if the difference is not significant the carryover effect may be ignored.

(3) Analysis of treatment–period interaction effects (or allocation effects or carryover effects)

D_A(1 – 2)_ – D_B(1 – 2)_ = 2(T_I_ – T_C_)

Compare D_A(1 – 2)_ and D_B(1 – 2)_ using an unpaired t-test, and test the difference between the treatment effect of EMLA Cream (T_I_) and that of Youpatch Tape (T_C_) for significance.

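### Section 14.1's 31 patients per group is slightly too low for its own inputs, and 34 enrolled does not quite cover the 10% end of the stated dropout range (minor)

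*Protocol*

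**What the plan says.** Section 14.1 (Rationale for Determination of Target Enrollment) gives four inputs:

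- a difference between drugs of 10 mm ("the use of EMLA Cream will increase VAS score by 10 mm compared with Youpatch Tape");
- "an intra-individual standard deviation in VAS improvement of 20 mm";
- "α for type 1 error (α error) as 5% on both sides";
- "80% power (1 – β").

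From these it concludes that "31 individuals are required in each group (62 in both groups"). After allowing for 5%–10% discontinuation or dropout, "the scheduled enrollment was set at 34 individuals per group (68 in both groups"). Section 9.1 repeats the total: "The total number of subjects to be enrolled in the study as a whole is 68 patients".

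The primary comparison is step (3) of the method of analysis for the primary endpoint in Section 14. It compares the Period I minus Period II differences, D, of the two sequence groups "using an unpaired t-test, and test the difference between the treatment effect of EMLA Cream". The protocol gives neither the sample-size formula nor the rounding rule.

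**The concern.** A number required for a given power has to be rounded up, and it should belong to the test that will be used. The protocol's figure looks like a normal-approximation result rounded down, with no allowance for the t-test. The dropout step also falls short at the top of its own range, because 34 less 10% is under 31. All three departures lower the power.

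The accuracy of a figure that will be reported is at stake. If the result is not significant, readers will judge it against 80% power with 62 completers, and the stated inputs do not quite support that.

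**Working it through.** **Inputs (Section 14.1).** Difference 10 mm; SD 20 mm, read as the within-patient SD of one period's VAS improvement; two-sided 5%; 80% power.

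**Quantities for the planned test (Section 14, step 3).** In the protocol's model, the mean of D differs between the groups by 2(T_I − T_C) = 2 × 10 = 20 mm. With independent within-patient errors of equal variance in the two periods, SD(D) = 20 × √2 = 28.3 mm.

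**1. The protocol's figure, normal formula.**
n per group = 2 × SD(D)² × (z₀.₉₇₅ + z₀.₈₀)² / 20² = 2 × 800 × (1.960 + 0.842)² / 400 = 31.40.
The stated 31 is this value rounded down; rounded up it is 32. Power with 31 per group:
SE = 28.28 × √(2/31) = 7.18; 20/7.18 = 2.784; Φ(2.784 − 1.960) = 79.5%.

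**2. Other readings of the 20 mm.**
- As the SD of D itself, 17 per group would suffice (80.7% by the t-test), and 31 per group would give 97.2%.
- As the SD in a parallel-group comparison, 63 per group would be needed.

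Of the readings tried, only the within-patient, single-period one leads to about 31.

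**3. The planned t-test (noncentral t, contrast 20 mm, SD 28.3 mm).**

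| Completers | Situation | Normal | t-test |
|---|---|---|---|
| 34 + 34 | no loss | 83.0% | 81.9% |
| 33 + 33 | smallest equal groups reaching 80% by t | 81.9% | 80.8% |
| 32 + 33 | 3 of 68 lost | – | 80.1% |
| 32 + 32 | 4 of 68 lost | 80.7% | 79.5% |
| 31 + 31 | stated requirement | 79.5% | 78.2% |
| 30 + 31 | 7 of 68 lost | 78.9% | 77.5% |

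**4. Dropout.**
- 5%: 34 × 0.95 = 32.3 per group (64.6 in total). Power by t is about 79.9% at the fractional count, and 79.5% or 80.1% at 64 or 65 patients.
- 10%: 34 × 0.90 = 30.6 per group (61.2 in total), below the stated 31 (62). Power by t is 77.5% with 61 completers.
- Inflating 31 for 10% loss gives 31/0.90 = 34.4, i.e. 35 per group.
- 34 per group keep at least 31 up to a loss of 1 − 31/34 = 8.8%.

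**5. Difference detectable with 80% power (t-test).** 10.06 mm with 64 completers, 10.23 mm with 62, 10.32 mm with 61.

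**The case against.** The strongest reply is that the plan's figure reproduces apart from rounding. The formula is right for the design, and no factor of two is missing. Planning with a normal formula and analysing with a t-test is common, and costs only 1.3 points here (79.5% against 78.2%). Both planning inputs are round numbers, and an SD of about 19.6 mm instead of 20 (20 × 10/10.23) would restore 80% with 62 completers. All of this stands, and it is why the point is minor.

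It can also be said that 10% is only the top of a range and that 34 per group hold 31 through most of it, including the 7.5% midpoint (31.45 remain). That is correct: at 10% the deficit against 31 is 0.4 of a patient per group.

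Finally, not every dropout need be lost to the analysis. Section 14.2 makes the Full Analysis Set primary, Section 7.3 calls for efficacy evaluation at discontinuation, and each period's score averages three punctures. The protocol does not say how partial data enter, so 61 is a lower bound on the usable number at 10% dropout.

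None of this makes 31 the number required for 80% power. The inputs, the test and the figure all stand in the protocol, so this is a misstated figure and not a detail left to the analysis plan.

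**Conclusion.** The point holds as a minor correction. By the protocol's inputs, 31 per group is one patient short by the normal formula and two short by the planned t-test. The stated 80% is then 79.5% or 78.2%. At the top of the dropout range, power by the t-test is about 77.5%, a shortfall of about 2.5 points.

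A reader might infer that the trial is underpowered or never had 80% power. The document does not support that. The 68 patients to be enrolled give 81.9% by the t-test if none are lost and about 80% at 5% loss. With 61–64 completers, the difference detectable with 80% power moves only from 10 mm to about 10.1–10.3 mm.

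The figures assume that 20 mm is the within-patient SD of a single period's improvement, that within-patient errors are independent with equal variance in the two periods, that the groups are equal or nearly so, and that dropouts contribute nothing. If 20 mm were the SD of D, there would be no shortfall, but then the stated 31 would be nearly twice the number needed.

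**What to change.** Keep 68 patients and restate Section 14.1, for example:

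> By the two-sided unpaired t-test on D (SD of D 28.3 mm, i.e. 20 mm × √2), 33 patients per group (66 in total) are required for 80% power at a difference of 10 mm. The 20 mm is the within-patient SD of a single period's VAS improvement, not the SD of the between-drug difference. With 68 enrolled and 5%–10% dropout, about 61–64 completers are expected. They give about 78%–80% power for 10 mm, or 80% power for about 10.1–10.3 mm.

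This replaces the statement that 31 per group (62) are required. It needs no extra patients and no change to the analysis. The cost is a wording amendment, with the approvals that Section 19.2 asks for, and a stated power up to about 2.5 points less favourable. Holding 80% by the t-test at 10% dropout would take 33/0.90 = 36.7, i.e. 37 per group (74 in total); a shortfall this small does not call for that.

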**Method of Analysis of Primary Endpoint**

The primary endpoint is analyzed by the standard statistical procedures^18)^ for a two-group, two-period crossover study.

Total effect of EMLA Cream in Group A (E_A1I_) = ΔVAS (Group A EMLA)

Total effect Youpatch Tape in Group A (E_A2C_) = ΔVAS (Group A Youpatch)

Total effect of EMLA Cream in Group B (E_B2I_) = ΔVAS (Group B EMLA)

Total effect Youpatch Tape in Group B (E_B1C_) = ΔVAS (Group B Youpatch)

Crossover design analysis

|  | Period I | Period II | Difference in effects | Sum of effects |
| --- | --- | --- | --- | --- |
| Group A | EMLA  E_A1I_ = T_I_ + P_I_ + TP_A_ | Youpatch  E_A2C_ = T_C_ + P_2_ + TP_A_ | D_A(1 – 2)_ = E_A1I_ – E_A2C_  = (T_1_ – T_C_） + (P_1_ – P_2_) | S_A(1 + 2)_ = E_A1I_ + E_A2C_ = (T_I_ + T_C_) + (P_1_ + P_2_) + 2TP_A_ |
| Group B | Youpatch  E_B1C_ = T_C_ + P_1_ + TP_B_ | EMLA  E_B2I_ = T_I_ + P_2_ + TP_B_ | D_B(1 – 2)_ = E_B1C_ – E_B2I_  = [ – (T_I_ – T_C_)] + (P_1_ – P_2_) | S_B(1 + 2)_ = E_B1C_ + E_B2I_ = (T_I_ + T_C_) + (P_1_ + P_2_) + 2TP_B_ |

E: Total effect: T: treatment effect; P: period effect; TP: treatment–period interaction effects (or allocation effects or carryover effects).

Subscripts: I: EMLA Cream; C: Youpatch Tape; 1: Intervention Period I; 2: Intervention Period II; A: Group A; B: Group B.

(1) Analysis of period effect

D_A(1 – 2)_ – ( – D_B(1 – 2)_) = D_A(1 – 2)_ – D_B(2 – 1)_ = 2(P_1_ – P_2_)

Test whether or not this is 0 by comparing D_A(1 – 2)_ and D_B(2 – 1)_ using an unpaired t-test, and if the difference is not significant the period effect may be ignored.

(2) Analysis of carryover effect

S_A(1 + 2)_ – S_B(1 + 2)_ = 2(TP_A_ – TP_B_)

Test whether or not this is 0 by comparing S_A(1 + 2)_ and S_B(1 + 2)_ using an unpaired t-test, and if the difference is not significant the carryover effect may be ignored.

(3) Analysis of treatment–period interaction effects (or allocation effects or carryover effects)

D_A(1 – 2)_ – D_B(1 – 2)_ = 2(T_I_ – T_C_)

Compare D_A(1 – 2)_ and D_B(1 – 2)_ using an unpaired t-test, and test the difference between the treatment effect of EMLA Cream (T_I_) and that of Youpatch Tape (T_C_) for significance.

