## Allocation Method and Allocation Adjustment Factors

Subjects are randomly allocated to treatment groups by the Study Coordinator at the time they are registered as study participants. To prevent any major bias in (1) age, (2) sex, (3) subjective symptoms, or other factors in the process randomization, the minimization method is used with these factors as adjustment factors.

1. **Study Design**

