**Method of Analysis of Secondary Endpoint**

Analysis of the change in health-related QOL [SF36 subscale score (0–100 points)] before and after treatment

The analysis will be carried out in the same way as for the primary endpoint.

1. **Monitoring**
   1. Conduct of Monitoring

Monitoring will be carried out to confirm that this study is being conducted safely and in accordance with the protocol and that data are being collected accurately. Monitoring will be carried out on the basis of the data recorded in Case Report Forms by the Kanazawa Medical University Clinical Trial Center in accordance with the institution's Monitoring Manual.

- 1. Specific Procedures for Monitoring

1) A monitor belonging to the Kanazawa Medical University Clinical Trial Center will be responsible for monitoring this study.

2) After the first patient has been registered, monitoring will be conducted to check eligibility, the method of obtaining consent, and the registration method. If this reveals problems, corrective action will be taken. Subsequently, unless any specific matters of concern arise, monitoring will be carried out after every 10th patient registration or every 12 months.

3) Monitoring will also be conducted as required should an unexpected serious adverse event occur or in cases with a major effect on the performance of the study.

4) The timing and nature of its conduct will be reviewed in accordance with the state of progress of monitoring.

5) The monitor will submit a Monitoring Report to the Principal Investigator immediately after monitoring has been conducted.

- 1. Matters to be Monitored

1. Confirmation of consent and eligibility
2. Status of implementation of the study
3. Protocol deviations
4. Serious adverse events
5. Adverse events and other problems concerning the progress and safety of the study
6. **Ethical Matters**
   1. Regulations to be Observed

All persons involved in this study must have thoroughly read and understood the WMA Helsinki Declaration and the Ethical Guidelines for Medical and Health Research Involving Human Subjects (MEXT/MHLW), to which all medical research on human subjects must conform, and comply with them in the conduct of the study.

- 1. Preparation and Revision of Patient Information Sheets and Consent Forms

A Consent Form is a document indicating a study subject's intention to participate in a clinical study.

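### Allocation is minimized on age, sex and subjective symptoms, but the primary and SF36 tests ignore these factors; the result is at worst a conservative test with a probably small loss of power, and adjustment is almost free

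*Protocol*

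**What the plan says.** **Allocation.** Protocol section 6.2 (Allocation Method and Allocation Adjustment Factors) states: "To prevent any major bias in (1) age, (2) sex, (3) subjective symptoms, or other factors in the process randomization, the minimization method is used". It calls the factors adjustment factors of the allocation. It gives no categories for subjective symptoms and leaves the list of factors open.

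**Primary analysis.** Section 14 (Method of Analysis of Primary Endpoint) forms, for each patient, the difference D between the effects in Period I and Period II, and their sum S. Each effect is a change in VAS from that period's own baseline. Period and carryover are checked with unpaired t-tests. In step (3) the treatment comparison sets D in Group A against D in Group B, "using an unpaired t-test, and test the difference between the treatment effect of EMLA Cream (T_I_) and that of Youpatch Tape (T_C_) for significance". No covariate or stratum term appears in any of the three tests.

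**Secondary analysis.** For SF36: "The analysis will be carried out in the same way as for the primary endpoint".

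**Planning values.** The target-enrollment rationale in section 14 assumes a 10 mm difference, "an intra-individual standard deviation in VAS improvement of 20 mm", a two-sided 5% level and 80% power. This gives 31 per group (62 in all), raised to 34 per group (68) for dropout.

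**The concern.** Minimization makes the two sequence groups more alike on the chosen factors than chance would. If a factor predicts D, the group difference in mean D then varies less from trial to trial than under simple randomization. The unpaired t-test does not know this. It keeps the factor's variation in its error term and reports the standard error that simple randomization would have produced.

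The consequences are confidence intervals that are too wide, a true type I error below 5%, and less power than a model containing the factors would have. Section 14 writes out the contrasts and names the test, so this is a choice that the protocol fixes and does not leave for later.

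**Working it through.** **Inputs.** From section 14: difference 10 mm, intra-individual SD 20 mm, two-sided α 0.05, power 80%, 31 per group. Assumed: R², the share of the variance of D explained by the minimization factors, because the protocol gives no figure. Range shown: 0 to 20% (to 30% in the simulation).

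**1. The protocol's sample size.** Read 20 mm as the SD within a patient per period.
- Total N = 2 × [20 × (1.960 + 0.842) / 10]² = 62.8, or 31.4 per group. The stated 62 is this figure rounded down.
- Reading 20 mm as the SD of the within-patient difference would give 16 per group, which does not match.
- Dropout: 62/0.95 = 65.3 and 62/0.90 = 68.9. The stated 68 lies between them.

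**2. Power of the planned test.**
- SD of D = 20√2 = 28.28 mm.
- By section 14's own algebra, D_A − D_B estimates 2(T_I − T_C), so the target difference is 20 mm.
- SE = 28.28 × √(2/31) = 7.18 mm. Noncentrality = 20/7.18 = 2.784 on 60 df.
- Power = 78.2% (noncentral t), or 79.5% with the normal approximation.

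**3. Power with the factors in the model.** Three factor terms leave 57 df. SE = 7.18 × √(1 − R²).

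| R² (assumed) | SE (mm) | Noncentrality | Power | Gain over 78.2% |
|---|---|---|---|---|
| 0 | 7.18 | 2.784 | 78.1% | −0.1 |
| 2% | 7.11 | 2.812 | 78.9% | 0.7 |
| 5% | 7.00 | 2.856 | 80.2% | 2.0 |
| 10% | 6.82 | 2.934 | 82.2% | 4.0 |
| 20% | 6.43 | 3.112 | 86.4% | 8.2 |

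**4. Simulation of the mechanism.** 62 patients, three balanced binary factors, minimization with probability 0.9 for the favoured group, 6000 runs per setting. Monte Carlo standard error is about 0.3 points for type I error and 0.5 points for power.

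*The factor shifts D equally in both sequences:*

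| R² | True SD of estimate / mean reported SE (null) | Type I error, planned / adjusted | Power, planned / adjusted |
|---|---|---|---|
| 0 | 7.16 / 7.14 | 5.0% / 5.1% | 78.5% / 78.5% |
| 10% | 6.82 / 7.16 | 4.2% / 5.2% | 79.0% / 82.1% |
| 20% | 6.37 / 7.16 | 2.8% / 4.7% | 79.9% / 85.6% |
| 30% | 6.02 / 7.17 | 2.1% / 4.7% | 81.9% / 90.5% |

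The planned test's own power rises slightly with R², because minimization does reduce the true variance. The simulated gap at 10% is therefore about 3 points, against 4 in step 3.

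*The factor only modifies the treatment effect (opposite slopes in the two sequences):* at R² of 10%, power is 78.4% planned and 78.3% adjusted; at 30%, 77.8% and 77.6%. Nothing is lost.

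**5. How large a factor effect each R² requires.** A balanced binary factor explaining R² alone separates mean D by 2 × √R² × 28.28 mm. With three equal, independent factors, each separates it by 2 × √(R²/3) × 28.28 mm.
- R² 2%: 8.0 mm alone, or 4.6 mm each for three.
- R² 5%: 12.6 mm, or 7.3 mm each.
- R² 10%: 17.9 mm, or 10.3 mm each.

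**The case against.** The strongest reply is that the crossover already removes most of what adjustment would remove. A factor's effect on pain level cancels when each period's baseline is subtracted. An equal effect on the response to both drugs cancels in D. What remains is a factor-by-period effect, and the protocol gives no reason to expect a large one between two one-week periods separated by a one-week wash-out. By step 5, an R² of 10% would need three factors that each move D by about as much as the planned treatment difference. This stands, and it limits the size of the point.

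A reader might also infer three stronger conclusions that the documents do not support:
- *That the test is invalid.* The error runs toward conservatism. No false positive and no bias follow.
- *That minimization leaves the trial short of its 80% power.* The 78.2% arises because 31 per group comes from a normal approximation rounded down. It would be the same under simple randomization. Where the factors do matter, the planned test's simulated power is 79% to 82%. The loss is relative to an adjusted analysis only.
- *That any relation between a factor and D costs power.* A factor that only modifies the treatment effect costs nothing.

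It can also be said that the covariates are not ready for use. Section 6.2 does not define the symptom categories, and the subject-data list in section 8.1 does not name them. This stands as well: the model must use whatever was entered in the allocation system, and the protocol should say what that is.

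The objection does not remove the mismatch. The protocol names factors important enough to allocate by, then fixes tests that ignore them.

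**Conclusion.** The point holds as a modest matter of efficiency. If a minimization factor shifts D in the same direction in both sequences, the planned t-test overstates its standard error and is conservative. The loss on the primary test is under 1 point of power at an R² of 2%, about 2 to 4 points at 5% to 10%, and nil at 0. The low end is the more plausible, because stable effects cancel.

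These sizes rest on the protocol's 10 mm and 20 mm, 31 evaluable patients per group, three factor terms, and an R² that is assumed. The same reasoning carries over to SF36 and to the carryover test on S. Factor effects on drug response do not cancel in S, so adjustment could gain more there. The protocol gives no SD for S or for SF36, so no size can be put on either.

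**What to change.** In section 14, replace the unpaired t-tests on D with a linear model of D on sequence group (Group A = 1, Group B = 0) plus the minimization factors as entered in the allocation system: age, sex and subjective-symptom category. Report half the sequence coefficient, with its 95% confidence interval, as the EMLA minus Youpatch effect. Use the same model for S and for SF36. Keep the plain t-test as a sensitivity analysis. In section 6.2, state the symptom categories and close the list of factors, so that the covariates are fixed before the data are seen.

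The cost is a few sentences and a few degrees of freedom (three if each factor takes one term). If the factors explain nothing, power falls by about 0.1 point (78.2% to 78.1%). The sample size does not need to change on account of this point.
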